## Methods/Design

The MARRES study is a multi-institution cohort study being conducted by KoREa-BSG. It is prospectively collecting clinical data from patients undergoing mastectomy and reconstruction in academic hospitals in Korea (Fig. 1). The version 1.71 protocol for this study was approved on June 27, 2022. The principal investigator (PI) will periodically review and evaluate study conduct and progress according to the study protocol; data collection status for participant safety; and the quality, consistency, security, and accessibility of the accumulated data at regular intervals during the study. The protocol and study progress will be audited annually according to the policy of each Institutional Review Board. The PI and sub-PIs meet to communicate every one or two months. Only the PI and sub-PIs will have access to the final trial dataset, but the dataset could be shared with the permission of the PI upon reasonable request. We will publish the results of the dataset in a medical journal.

**Fig. 1 Fig1:**
[figure not shown]
Flowchart of the prospective cohort study

The inclusion criteria for the patients are as follows: adult women older than 19 with breast cancer or a high risk of breast cancer (patients with *BRCA1/2*, *TP53*, *PALB2* mutations, etc.) who are scheduled for a therapeutic or risk reducing mastectomy and want immediate reconstruction. The PI or a physician delegated by the PI provides information about the study and an adequate opportunity to consider all options to all potential trial participants and obtains signed informed consent forms before enrollment. Patients who plan breast-conserving surgery or who are not candidates for IBR will be excluded. The target number of enrolled patients is 2000.

Patients' clinicopathological factors, including height and weight, will be collected, along with data on surgical results, including photographic and oncological results and cost-effectiveness and patient satisfaction data. The basic characteristics, photographs, and satisfaction of patients will be collected preoperatively using the Breast-Q survey. Patient data will be collected within 6 months of surgery, including clinicopathological factors, surgery results (drainage amount, removal date, and complications), postoperative recovery evaluations, complications and adverse reactions, and cost. Between 6 months and 1 year after surgery, the results of surgery, recurrence, a satisfaction survey, intraoperative console video, and postoperative photographs will be collected. Every 12 months thereafter, data on adjuvant therapy (chemotherapy, radiation therapy, targeted therapy, and endocrine therapy), surgical results, recurrence, adverse events, and other unintended effects of the interventions will be investigated and collected until the end of the study period.

Personal information that can identify the subjects will be kept confidential even after the publication of the study. After enrollment, each participant’s name will be encrypted and replaced with a participant number. The datasets collected from each institution will be accumulated and stored in a designated computer on a central server. Access to that database is restricted to authorized researchers.

An interim analysis will be done after the recruitment of subjects is completed, no later than the 3rd year after the start of data collection. The PI will access those interim results and report them to the all sub-PIs. At that time, the PI and sub-PIs will determine whether the trial should be terminated.

Follow-up observation and data collection of the subjects will continue for 4–8 years after enrollment, and then the final analysis will be conducted. All patients will be guided to complete follow-up evaluations indicating recurrences and survival for at least 5 years.

### Timeline

Actual Study Start Date: April 8, 2020Estimated Primary Completion Date: April 7, 2025Estimated Study Completion Date: April 7, 2030

### Study population

Intervention details.

#### Procedure: Robotic nipple-sparing mastectomy

Patients undergoing RNSM and IBR are enrolled in this arm. RNSM should be performed using a robotic surgical system (da Vinci S, Si, X, Xi, or SP). Axillary or lateral incisions are used for this procedure.

Other names: Robot-assisted nipple-sparing mastectomy, robot mastectomy, robotic mastectomy, hybrid robotic nipple-sparing mastectomy, robot-assisted nipple-areolar complex, and skin-sparing mastectomy.

#### Procedure: Endoscopic nipple-sparing mastectomy

Patients undergoing ENSM and IBR are enrolled in this arm. ENSM should be performed using endoscopic tools for mastectomies [51].

Other names: Endoscopy-assisted nipple-sparing mastectomy, endoscopic-assisted nipple-sparing mastectomy, endoscopic nipple-sparing mastectomy, endoscopic subcutaneous mastectomy, video-assisted nipple-sparing mastectomy, endoscopic video-assisted breast surgery, videoendoscopic nipple-sparing mastectomy.

#### Procedure: Conventional mastectomy (including nipple-sparing mastectomy, skin-sparing mastectomy)

Patients undergoing a CM and immediate reconstruction are enrolled in this arm. CM should not be performed using a robotic or endoscopic surgical system. Any incisions can be used for this procedure. CM also includes NSM and SSM.

Other names: Total mastectomy, mastectomy, nipple-sparing mastectomy, skin-sparing mastectomy.

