**Discussion:**

This study will provide evidence about the surgical outcomes, oncologic outcomes, and patient satisfaction with RNSM and endoscopic nipple-sparing mastectomy (NSM), compared with conventional NSM.

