### Evidence for immediate reconstruction

#### Guidelines and reviews for conventional NSM (CNSM) with IBR

The first NSM was described by Freeman in 1962 but only for RRM [20]. Subcutaneous mastectomy for patients with primary breast cancer was first reported by Hinton et al. in 1984 and showed rates of local recurrence and survival comparable to those with CM [21]. The use of NSM for women with breast cancer has been justified by demonstrating its oncologic and surgical safety. Previous studies confirmed acceptable locoregional recurrence, disease-free survival, and overall survival (OS) rates following NSM [4, 22–27]. The surgical outcomes of NSM, including rates of nipple necrosis and overall postoperative complications, were acceptable in previous reports [4, 22, 23]. The procedure’s advantages in terms of better aesthetic outcomes, improved patient satisfaction, and psychosexual benefits have also been investigated [28–30].

The National Comprehensive Cancer Network (NCCN) guideline comments that SSM showed similar oncologic outcome compared to CM [31]. However, SSM should be performed by an experienced breast surgeon. Similarly, NSM is comparable oncologic outcome to SSM, if cases are appropriately selected. NSM can be performed for any tumor size independent of axillary status, especially for early breast cancer, and for ductal carcinoma in situ and RRM, but having cT4b and cT4c breast cancers with skin involvement or skin edema, and clinical signs of nipple involvement and any R1 resection at the nipple margin should be a contraindication.

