### Statistical analyses

We have categorized three study sets: Conventional vs. endoscopic, conventional vs. robotic, and conventional vs. endoscopic and robotic. Additionally, subgroup analyses of a randomized registry trial will be conducted to compare the surgical and oncologic outcomes between the conventional and minimally invasive (endoscopic and robotic) groups. Primary and some secondary outcomes (postoperative complications, the satisfaction of patients and surgeons, and the cost-effectiveness evaluation) and other categorical variables will be examined by the chi-square test or Fisher's exact test. Continuous variables will be examined by t-testing or ANOVA and Mann–Whitney testing or Kruskal–Wallis testing, if needed. The other secondary outcomes (RFS, OS, and cancer incidence rates in 5 years) will be examined using Kaplan–Meier plots and log-rank testing. No imputation will be performed for subjects who have missing data due to dropping out of the study. Data relating to major protocol non-adherence due to patients dropping out of the study will be excluded from the analysis population.

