## Discussion

This study will provide evidence about the surgical outcomes, oncologic outcomes, and patient satisfaction with RNSM and ENSM, compared with CM.

This prospective cohort study has some advantages over previous retrospective studies conducted in a single center or with a single surgeon. The sample size of the study is larger than previously published studies of RNSM. Additionally, our protocol will collect large-scale PRO data about cosmesis after RNSM. The participation of many surgeons from multiple institutions will allow us to observe the effects of different surgeons or institutions on the clinical outcomes of the surgical procedures. In Korea, an increasing number of breast surgeons has been performing RNSM because of active educational programs and systematic research activities. Therefore, the involvement of many skilled surgeons will produce accurate clinical outcomes for the procedures. However, because this is not a randomized controlled trial, selection bias might still occur in determining the surgical modality for each subject. To overcome that limitation and secure the surgical and oncologic outcomes from a new, innovative surgical procedure, we are planning a randomized controlled trial for the near future.

Through this study, we wish to confirm that minimally invasive breast surgery can be considered as a standard treatment for women with breast cancer and as a preventive treatment for women with a high risk of pathogenic variants.

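### The conventional arm pools nipple-sparing, skin-sparing and total mastectomy, but the robotic and endoscopic arms are nipple-sparing only, so the three main comparisons mix surgical approach with mastectomy type

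*Protocol article*

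**What the plan says.** The arm definitions are in the intervention details of the protocol article. For the robotic arm: "Patients undergoing RNSM and IBR are enrolled in this arm". For the endoscopic arm: "Patients undergoing ENSM and IBR are enrolled in this arm". Both are nipple-sparing by definition. The conventional arm is defined by the absence of robot and endoscope, with any incision allowed: "CM also includes NSM and SSM". Its synonym list is wider still: "Other names: Total mastectomy, mastectomy, nipple-sparing mastectomy, skin-sparing mastectomy". The eligibility criteria likewise admit conventional and skin-sparing mastectomy (SSM).

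The comparator is stated in two ways:

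- The Discussion paragraph of the abstract describes the robotic and endoscopic procedures as "compared with conventional NSM". Table 2 lists conventional NSM as the comparator in the row for this study.
- The main Discussion promises evidence on outcomes and "patient satisfaction with RNSM and ENSM, compared with CM", where CM is conventional mastectomy. Statistical analyses sets up three study sets, "Conventional vs. endoscopic, conventional vs. robotic, and conventional vs. endoscopic and robotic", each using the conventional group undivided.

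The tests named there are chi-square or Fisher, t-test or ANOVA or their rank equivalents, and Kaplan–Meier with log-rank. No restriction to NSM, and no stratification or adjustment for mastectomy type, is stated. The 1:1 match in Pre-specified subgroup analysis names no matching variable.

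**The concern.** If one arm is nipple-sparing throughout and the other is a mixture, a difference between them may come from the robot or endoscope, from keeping the nipple, or from both. The planned tests cannot separate these.

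The article gives its own reasons to think that type matters:

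- The Background says NSM gives better satisfaction and cosmetic results than SSM.
- The section on conventional NSM names nipple necrosis among the outcomes of NSM. That complication cannot occur where the nipple is removed, yet the first primary endpoint pools all complications.
- The surgeon's cosmetic score in Secondary endpoints includes symmetry of the nipple-areolar complex, which does not mean the same thing in a woman whose nipple was not kept.

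What is at stake is interpretation. A reader of the abstract would take the result as robotic or endoscopic NSM against open NSM, and the analysis as planned would not estimate that.

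**Working it through.** **Step 1. Is there an arithmetic fault?** No. The plan gives no figure for the make-up of the conventional arm. Its one complication calculation is the 112-patient matched subgroup: reference rate 34.8%, robotic rate 17.1%, margin 0.05, one-sided 0.025, 80% power, unpooled Z.

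- Variance term: 0.348 × 0.652 + 0.171 × 0.829 = 0.2269 + 0.1418 = 0.3687
- Distance from the margin: 0.05 + (0.348 − 0.171) = 0.227
- n per arm = 0.3687 × (1.960 + 0.842)² / 0.227² = 56.15, or 112.3 in total

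Exact enumeration at 56 per arm gives a significance level of 0.0265 and power of 0.800, as the article states. The point is about what is compared, not about this sum.

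**Step 2. The passages side by side.**

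- Robotic arm: NSM only.
- Endoscopic arm: NSM only.
- Conventional arm: NSM, SSM and total mastectomy.
- Comparator in the abstract and Table 2: conventional NSM.
- Comparator in the three study sets and the main Discussion: all conventional mastectomy.

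Under either stated comparator, approach and mastectomy type differ together between the groups analysed.

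**Step 3. What the mixture does to a complication rate.** Let w be the non-NSM share of conventional patients, and D the complication rate in non-NSM minus that in NSM controls. The conventional arm then has rate p + wD, where p is the conventional NSM rate. If approach has no effect, the expected robotic-minus-conventional difference is p − (p + wD) = −wD.

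The article gives neither w nor D, nor the sign of D. The following values are assumptions, chosen only to show how the formula behaves:

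- w = 10%, |D| = 5 points: shift of 0.5 points
- w = 30%, |D| = 10 points: shift of 3 points
- w = 50%, |D| = 10 points: shift of 5 points

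Each can go in either direction, and the shift is zero if D is zero.

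**Step 4. What that could do to an unadjusted test.** Further assumptions: an NSM rate of 34.8% (the reference rate quoted for grade III complications, borrowed here only to set a level), 1000 against 1000 patients, no true effect of approach, and a two-sided 5% test.

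Worked case, w = 30% and D = −10 points:

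- Conventional rate: 0.348 − 0.030 = 0.318; pooled rate 0.333
- Null SE: √(0.333 × 0.667 × 0.002) = 0.0211, so the critical difference is 1.96 × 0.0211 = 0.0413
- Alternative SE: 0.0211
- Φ((0.030 − 0.0413) / 0.0211) ≈ 0.296, and the opposite tail is negligible

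Across w from 10% to 50% and |D| from 5 to 10 points, rejection runs from 5.6% to between 64% and 67% (depending on the sign of D). With 300 against 1700 patients it runs from 5.3% to 41%. These figures show that the mixture can matter. They do not estimate the bias in this study.

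**The case against.** The strongest reply is that this is a cohort described as exploratory, sized without a statistical calculation and open to all mastectomy types. Minimally invasive surgery against conventional mastectomy with reconstruction is a coherent question, and the arm definition, eligibility, study sets and main Discussion all fit it. The contrary wording is one sentence of the abstract and one table row. The article also concedes selection bias in the choice of modality, and an analysis plan that is not shown might adjust for type. This lowers the weight of the point but does not remove it. The comparator and study sets are fixed here, the two statements of the question conflict, and the admitted selection bias concerns modality, not mastectomy type.

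The robotic arm's synonym list ends with a mention of skin-sparing mastectomy. It reads most naturally as part of one name that also covers the nipple-areolar complex, and the arm definition remains nipple-sparing.

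A reader might also infer more than the text supports:

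- **That the bias can be set against the 5-point margin.** That margin belongs to the 112-patient subgroup and to grade III complications. The article does not say how often nipple complications reach grade III, or that other complications are equally frequent across types.
- **That the conventional arm must look safer.** The absence of nipple complications pulls that way, but other complications may differ in either direction. A lower control rate would also make non-inferiority harder to show, not easier.
- **That recurrence-free survival must look worse in the conventional arm.** The background review says "clinical signs of nipple involvement and any R1 resection at the nipple margin should be a contraindication", so some women unsuited to NSM could be found only among the controls. But this is guideline text, not an eligibility or allocation rule, and a positive nipple margin is known only after resection. The Background calls NSM and SSM oncologically comparable.
- **That the patient-satisfaction endpoint is clearly biased.** The BREAST-Q scales named cover abdomen, back and implants. None is a nipple scale, so the general advantage of NSM may not carry over to them.

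**Conclusion.** The point holds as one of comparator and analysis-set definition. As written, the three main comparisons combine the effect of approach with that of mastectomy type, and so do not estimate the contrast named in the abstract and Table 2. The size and direction of the resulting bias are unknown: they depend on the non-NSM share of controls and on outcomes by type, and the article gives neither. The 0.5 to 5 point range is conditional on assumed inputs and should not be quoted as an estimate. The documents support neither a comparison with the non-inferiority margin nor a claim of worse recurrence-free survival in the conventional arm. This should be fixed before analysis. It does not call for a change to enrolment or treatment.

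**What to change.** Define conventional NSM, meaning the nipple-sparing subset of the conventional arm, as the comparator for the three study sets and for both primary endpoints. Report conventional skin-sparing and total mastectomy as a separate group. Keep all conventional against minimally invasive surgery as a secondary analysis, labelled as differing in mastectomy type. Require controls in the matched subgroup to be nipple-sparing. Align the abstract, Table 2, the conventional-arm description, Statistical analyses and the Discussion.

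The cost is wording and a smaller control group. With a non-NSM share w, a fraction 1 − w of conventional patients remains. For the matched subgroup, 56 NSM controls would need 56/0.9 = 62.2 (so 63), 56/0.7 = 80 or 56/0.5 = 112 conventional patients at assumed w of 10%, 30% or 50%, provided the 34.8% reference rate applies to NSM. The article does not say which type of mastectomy that reference group had.

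Two conditions apply. Mastectomy type must be captured in the surgical data, which the article does not state explicitly and which should be confirmed. And the restriction removes only this source of bias: selection of approach among women having NSM remains.

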### Endpoints

#### Primary endpoint

Postoperative complication rates within 30 postoperative days: Postoperative complication rates are calculated as the total number of postoperative complication cases per total operation cases.

Clavien-Dindo grade of postoperative complications in 180 postoperative days: The Clavien-Dindo grade of postoperative complications is evaluated. Only grade III or higher postoperative complications are used for this analysis.

#### Secondary endpoints

Recurrence-free survival (RFS) in 5 postoperative years: RFS events include locoregional recurrence, distant recurrence, and death by any cause. Contralateral breast cancer and a second primary malignancy are considered to be censored data.

Cancer incidence rate in 5 postoperative years: Cancer incidence rate for those who underwent a prophylactic mastectomy.

Patient satisfaction with reconstruction results preoperative (baseline) and 6 to 12 postoperative months: Reconstruction module with pre- and postoperative scales for satisfaction with the abdomen, as assessed by BREAST-Q version 2.0. (This scale should be completed only by patients who have had reconstruction using a TRAM flap or DIEP flap. Otherwise, it is skipped.) Satisfaction with the back, as assessed by BREAST-Q version 2.0. (This scale should only be completed by patients who have had reconstruction using an LD flap. Otherwise, it is skipped.) Satisfaction with implants, as assessed by BREAST-Q version 2.0. (This scale should only be completed by patients who have had reconstruction using implants. Otherwise, it is skipped.) In all scales, higher scores reflect better outcomes.

Surgeon's satisfaction with surgery within 6 postoperative months: Assessed using scoring criteria for cosmetic assessment [52], response options (overall symmetry, postoperative scar, NAC symmetry, etc.), and range (0–10). Higher scores reflect better outcomes.

Evaluation of the cost-effectiveness of the definitive surgery according to the surgical method: Assessed by conducting a patient’s survey 6 months to 1 year after the last surgery. This evaluation uses the EuroQol five-dimension scale, Korean version questionnaire. In all scales, higher scores reflect better outcomes.

### Inclusion & exclusion criteria

Inclusion Criteria:Female patients older than 19Patients with breast cancer or a high risk of breast cancer (*BRCA1/2*, *TP53*, *PALB2* mutations, etc.)Patients scheduled for a therapeutic or risk reducing mastectomy (including conventional, skin-sparing, and areolar-conserving mastectomies)Patients who want immediate reconstructionPatients who provide written consent to participate in the study

Exclusion Criteria:Patients scheduled for a breast-conserving surgeryPatients who do not want immediate reconstruction during mastectomyPatients who undergo a different procedure on the other side breast simultaneously

Surgeon Inclusion Criteria:Surgeons who are members of KoREa-BSGSurgeons who participated in an education program for RNSM as an operator more than once

### Stopping criteria

Patients are free to withdraw from the study at any point without limitation. All data collected before the withdrawal will be included. After a withdrawal, no additional data will be collected from that patient. If the PI determines that it is inappropriate to continue the clinical trial, some part or the entire study could be stopped.

### Sample size determination

We determined the sample size for this study according to the real clinical experience of the PI, without statistical calculation, to explore the safety and effectiveness of the robotic surgical system and derive clinical outcomes from the procedures. The main institution performed 4038 cases of breast surgery and 746 cases of mastectomy and IBR (18.5%) between 2016 and 2018, including 86 RRMs (86/746, 11.5%). The iBRA study reported the uni- or bilateral RRMs accounted for 34.8% of mastectomies [53]. The mean value of the RRM rate between the main institution and the iBRA study was 23.15%. We estimated an approximate sample size of 11.5% for the main institution and 23.15% for the other institutions.Planned enrollment is 2000 total patients across the conventional, endoscopic, and robotic groups.

### Pre-specified subgroup analysis

Because of the long duration and expensive cost of a randomized trial, we will extract random patients from our prospective cohort and conduct subgroup analyses as a randomized registry trial. In a previous study, the rates of grade III complications in the reference group and the robotic group were 34.8% and 17.2%, respectively. For the comparison of complication rates among different surgical methods, the required sample size was calculated as 112 (1:1 random match) according to the method used in a randomized registry trial previously introduced to detect a non-inferiority margin difference, which achieved 80% power between the group proportions of 0.0500. The robotic group proportion is assumed to be 39.8% under the null hypothesis of inferiority. The power was computed for the case in which the actual robotic group proportion is 17.1%. The test statistic used is the one-sided Z test (unpooled). The significance level of the test was targeted at 0.0250. The actual significance level achieved by this design is 0.0265.

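### The planned randomised registry trial is a random sample of 112 patients from a cohort in which surgery was not randomised, so its non-inferiority result would be observational and imprecise

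*Protocol article*

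**What the plan says.** All references are to the protocol article.

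- **Pre-specified subgroup analysis.** Citing the length and cost of a randomised trial, the plan states: "we will extract random patients from our prospective cohort and conduct subgroup analyses as a randomized registry trial". On size: "the required sample size was calculated as 112 (1:1 random match", with no matching variables named. The planning rates come from an earlier study: "the rates of grade III complications in the reference group and the robotic group were 34.8% and 17.2%, respectively". The null is set by "The robotic group proportion is assumed to be 39.8% under the null hypothesis of inferiority", which is 34.8% plus a 5-point margin. On the alternative: "The power was computed for the case in which the actual robotic group proportion is 17.1" percent. The test is a one-sided unpooled Z test with a target level of 0.0250 and a stated actual level of 0.0265.
- **Statistical analyses.** Three comparisons are planned: conventional against endoscopic, against robotic, and against both together. In addition, "subgroup analyses of a randomized registry trial will be conducted to compare the surgical and oncologic outcomes between the conventional and minimally invasive" groups, the latter defined as endoscopic plus robotic. Complications are to be tested by chi-square or Fisher's exact test.
- **Discussion.** The limitation is acknowledged: "because this is not a randomized controlled trial, selection bias might still occur in determining the surgical modality for each subject". A separate randomised trial is said to be planned.
- **Table 2.** The entry for this study under randomization is No.
- **Study population.** Patients enter the arm of the operation they undergo.

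**The concern.** In a registry-based randomised trial, treatment is allocated at random among registry patients. Here the operation has already been settled by other means, and chance decides only who is analysed. That does not break the link between choice of operation and patient, tumour, surgeon or hospital. The label therefore claims a property the design lacks, and it conflicts with Table 2 and the Discussion.

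This is the only analysis in the article with a margin, a significance level and a power; the section on sample size says the 2000 was set without statistical calculation. A non-inferiority result from it is thus the one most likely to be read as confirmatory. It would rest on 56 patients per group, would vary with which patients the draw happened to select, and would be confounded to an unknown degree. The section that sizes the analysis and the section that describes how it will be done also disagree on what is compared and how.

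**Working it through.** **1. Inputs, all from Pre-specified subgroup analysis.** Reference rate 0.348; robotic rate for power 0.171; margin 0.05; one-sided level 0.025; power 0.80; total 112 at 1:1.

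**2. Reproducing the plan's figure.**

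n per group = (1.960 + 0.842)² × [p_c(1 − p_c) + p_r(1 − p_r)] / (margin + p_c − p_r)²

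= 7.849 × (0.348 × 0.652 + 0.171 × 0.829) / (0.05 + 0.177)²

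= 7.849 × (0.2269 + 0.1418) / 0.0515 = 56.2

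This agrees with 56 per group, 112 in total. Exact binomial enumeration of the unpooled Z test with 56 per group gives:

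- power 80.0% at 34.8% against 17.1%
- level 0.0265 at 34.8% against 39.8%

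Both match the article. If 112 were the size of each group, power would be 97.7% and the level 0.0260, so 112 is the total.

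**3. What the 80% depends on.** The assumed advantage is 34.8 − 17.1 = 17.7 points, so the assumed truth lies 22.7 points from the null. Exact power with 56 per group and the reference fixed at 34.8%:

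| True robotic rate | Advantage (points) | Power |
|---|---|---|
| 17.1% | 17.7 | 80.0% |
| 17.2% | 17.6 | 79.6% |
| 20% | 14.8 | 66.9% |
| 25% | 9.8 | 41.8% |
| 30% | 4.8 | 20.9% |
| 34.8% | 0 | 8.6% |

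**4. Precision at equal rates of 34.8%.** With 56 per group, SE = √(2 × 0.2269 / 56) = 0.0900, so the 95% half-width is 1.96 × 0.0900 = 17.6 points, about 3.5 times the margin.

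For comparison, the cohort of 2000 with no endoscopic patients taken out and no adjustment. The article does not state the group split, so two are assumed:

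- 1000/1000: SE = √(2 × 0.2269 / 1000) = 0.0213; half-width 4.2 points; power 65%
- 1600/400: SE = √(0.2269/1600 + 0.2269/400) = 0.0266; half-width 5.2 points; power 47%

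Eighty percent power at equal rates would need 7.849 × 2 × 0.2269 / 0.05² ≈ 1425 per group (2850 in total), more than the whole cohort.

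**5. Whether anything is randomised.** The arm definitions, Table 2 and the Discussion all describe surgery that was not allocated by chance. A simple random draw within each operation group has, in expectation, the same covariate distribution as that group. The expected bias of the difference is therefore the cohort's, with more sampling error.

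**6. The two sections side by side.**

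| | Pre-specified subgroup analysis | Statistical analyses |
|---|---|---|
| Contrast | Robotic vs reference | Conventional vs endoscopic plus robotic |
| Outcome | Grade III complications, no time window given | Surgical and oncologic outcomes |
| Test | One-sided non-inferiority Z test | Chi-square or Fisher for complications |

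The robotic rate is also 17.2% where the earlier study is described and 17.1% in the power statement.

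**The case against.** The strongest defence has four parts.

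- **Matching.** The article is a condensed account and refers to a random match by a previously introduced method. Matching variables may be in the full protocol, and matching on them could reduce measured confounding. This stands. A reader might infer that the subset removes no selection bias at all, and the article does not support so firm a claim. Covariate matching would still not be random allocation, so the label remains wrong.
- **Disclosure.** The study is called exploratory, and the Discussion admits it is not randomised and that selection bias may occur. This makes misreporting less certain. It also means the article contradicts its own label.
- **The power assumption.** A non-inferiority test may be sized on an expected benefit. The assumption is openly stated, is attributed to earlier data and is computed correctly. It is therefore an optimistic assumption, not an error, and the table above shows how much rests on it.
- **Additional analysis.** A reader might infer that 94% of the data are thrown away, since 112/2000 = 5.6%. The article does not support that. The Statistical analyses section also compares the groups across the cohort, and endoscopic patients could not enter a robotic against reference comparison. The share of eligible patients left out cannot be computed without the group sizes.

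A reader might also object to the 0.0265 level. It is disclosed and exceeds the target by only 0.0015, so it does not carry the point. Nor does the Statistical analyses section claim that 112 patients power the pooled or oncologic comparisons; the fault there is the inconsistency.

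**Conclusion.** The point holds in this form: the analysis is a random sample from a non-randomised cohort and should not be called randomised. It addresses a 5-point margin with a half-width of about 17.6 points at equal rates. Its correctly computed 80% power requires a robotic rate about 17.7 points or more below the reference, and falls to 41.8% at 25%, 20.9% at 30% and 8.6% at equal rates. Contrast, outcome and test differ between the two sections that describe it.

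The lack of randomisation follows from the text alone. The power figures assume a reference rate of 34.8%; the Sample size determination section gives the identical figure as a share of risk-reducing mastectomies in an external study, so its source is worth checking. The cohort figures rest on assumed splits and make no allowance for endoscopic patients or for weighting.

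**What to change.** - Remove the randomised label and the random extraction wherever they appear.
- Run the 5-point non-inferiority comparison, robotic against conventional, on all eligible cohort patients. Use a covariate-adjusted or propensity-weighted risk difference with a 95% confidence interval, described as observational.
- Reconcile the contrast, outcome (including its time window) and test between the Pre-specified subgroup analysis and Statistical analyses sections, and the 17.2% and 17.1% robotic rates.
- Replace the statement of 112 patients and 80% power with precision or power over a range of robotic rates, for example 17% to 35%. State the assumed group split and allow for the loss of effective sample size from weighting.

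The cost is wording and analysis code; no new patients or data are needed. The downside is that the randomised label is lost and power at equal rates may stay well below 80%: about 47% unadjusted with a 1600/400 split and 65% with 1000/1000, before any loss from weighting.
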